#### Sample size

Based upon existing data in the literature, a power of 0.8, and a *p*-value set at 0.05, with 20 women per group, we will be able to detect a mean difference of at least 0.37 standard deviation units in follicular levels of C-reactive protein and of insulin. In our previous study, we found follicular fluid CRP differences of 3.2 μg/ml (2.7 vs. 5.9 μg/ml, respectively) between normal weight and obese women [12]. Thus, we are confident that this sample size will be sufficient to detect clinically meaningful differences. Based on our experience, we expect that we will be unsuccessful in obtaining a good quality oocyte from approximately 33% of women enrolled. Therefore, we will enroll 30 women in each of the 4 groups (PCOS- standard of care, PCOS-intervention, no PCOS- standard of care, no PCOS-intervention) to assure that we will have at least 20 oocytes per group.

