#### Dietary intervention

The dietary intervention is based on the Mediterranean diet. The meal plan was designed by a Registered Dietitian and follows the 2015 Dietary Guidelines for Americans healthy Mediterranean-style eating pattern (Tables 2 and 3) [31]. Participants will be provided with all meals (3 meals/day) throughout the 8–12-week intervention that are in compliance with the Mediterranean diet in the form of refrigerated packaged meals from a company with the capacity to provide made-to-order meals and deliver them to the participant’s home address. The meals will be heated using conventional equipment found in most households and require no further preparation. Depending on calorie and macronutrient requirements, as assessed by the coach in accordance with participant feedback, snacks that adhere to the Mediterranean meal plan may be added. Snacks will include nutrient dense foods such as whole grains, fruits, nuts, low-fat milk, yogurt, and/or cheese. This nutrition intervention is not designed for participants to lose weight, however with the meal plan that could occur. Participants will be provided with a detailed weekly meal plan and will be asked to keep record of what they eat daily, on paper and/or using RedCap surveys.

**Table 2 Tab2:** Dietary Guidelines for Americans Mediterranean-Style Meal Pattern

Food Group	Daily Goal^a^
Vegetables	2.5 c-eq.
Fruits	2 c-eq.
Grains	6 oz.-eq.
Dairy	2 c-eq.
Protein	6 oz.-eq.
Oils	24 g

^a^Expressed as cup-equivalents or ounce-equivalence in accordance with the Dietary Guidelines for Americans standard practice [32]

**Table 3 Tab3:** Example menu day

Meal	Food Group Pattern^a^	Example Menu Items
Breakfast	1 c-eq fruit	1 Medium Apple
	2.8 oz.-eq grains	1 Blueberry Bagel
	1 c-eq dairy	2 Low-fat Cream Cheese Wedges
	1 oz.-eq nuts	1 Snack Pack Mixed Nuts
Lunch	2.5 c-eq vegetables, 1.3 oz.-eq grains, and 5.5 g oils^b^	Pesto Pasta with Sautéed Greens, Carrots, Tomato, and Zucchini Mixed Dish
Dinner	4 oz.-eq protein	Salmon
	2.5 c-eq vegetables, 1.3 oz.-eq grains, and 5.5 g oils^b^	Smoked Paprika Vegetables (sautéed broccoli, carrots, kale, and tomato), and Brown Rice Mixed Dish
	13.5 g oils	1 TB Olive Oil
Snack	1 c-eq fruit	2 Clementines
	0.6 oz.-eq grains	5 Multi-Grain Crackers
	1.1 c-eq dairy	2 Light String Cheese Sticks
	1 oz.-eq protein	3 Slices Deli Turkey Breast

^a^Equivalents are obtained through NDSR and rounded to the nearest tenth

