#### Statistical analyses

Prior to inferential analyses, exploratory data methods will be used to check for potential outliers and aberrant observations and measurements. The following will be tested between the PCOS and no PCOS groups to assess potential differences: fertility diagnosis (male factor, ovulatory disorder, tubal factor, endometriosis or unexplained), pregnancy, live birth, age and race using Mann-Whitney U nonparametric tests for each strata. Follicular fluid and serum metabolites will be analyzed using a one factor Analysis of Covariance (ANCOVA) at four levels because of the potential unbalanced data structure. Pair-wise comparisons using Tukey-Kramer post-hoc tests will be used to identify groups whose means differ significantly while retaining the family-wise error rate at 5%. If the distributional assumptions for ANOVA are not met, and if a suitable data transformation is not found, a Kruskal-Wallis equality-of-populations rank test will be used, followed by Dunn’s test of multiple comparisons. When the design is balanced, two-way ANOVA or non-parametric Friedman test will be used in data analysis. As alternatives, generalized linear models may be also used to test the effects of treatment and presence of PCOS and ANCOVA may also be used to control for additional confounding factors Correlations will be determined using the Pearson Product Moment or the Spearman Rank Order for non-parametric tests. Significance will be set at *p* < 0.05. RNA-seq data will be analyzed using SeqMonk and R software. Gene expression levels will be expressed as raw read counts for differential expression analysis and as log-transformed normalized reads per kilobase per million mapped reads for visualization. Differentially expressed gene expression will be identified using the DESeq2 package and filtered at ± two-fold change and statistical significance with a *p* value ≤0.05. Gene Ontology (GO), transcription factor (TF) target analysis, and pathway analyses will be conducted with DAVID bioinformatics and/or WebGestalt, which include multiple testing corrections. For participants assigned to the standard of care whose fertility treatments were unsuccessful, they will be offered to re-enroll and be directly assigned to the intervention group. The data from these participants will be analyzed separately, using paired t-tests or non-parametric equivalent to evaluate the effect of the intervention (pre and post).

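### With 20 women per group the trial cannot detect a 0.37 SD mean difference at 80% power; the planned analyses detect about 0.63 to 1.10 SD

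*Protocol article*

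**What the plan says.** The Sample size section of the protocol article gives its inputs and result in one sentence: at power 0.8 and p = 0.05, "with 20 women per group, we will be able to detect a mean difference of at least 0.37 standard deviation units" in follicular CRP and insulin. It names no test and does not say whether the test is one- or two-sided.

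It then cites a difference of 3.2 μg/ml in follicular fluid CRP (2.7 v 5.9) between normal-weight and obese women in an earlier study, and concludes: "Thus, we are confident that this sample size will be sufficient to detect clinically meaningful differences".

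The enrolment target follows from expected loss: "we will be unsuccessful in obtaining a good quality oocyte from approximately 33% of women enrolled", and so "we will enroll 30 women in each of the 4 groups".

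The Statistical analyses section sets the analysis: "Follicular fluid and serum metabolites will be analyzed using a one factor Analysis of Covariance (ANCOVA) at four levels", followed by Tukey-Kramer pairwise tests that hold the family-wise error at 5%. Two-way ANOVA (if the design is balanced) and generalized linear models for treatment and PCOS are also named.

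**The concern.** With 20 per group, a detectable difference below 0.4 SD is far smaller than a standard two-group calculation allows. Follicular fluid metabolites are a primary outcome in the Abstract, and this is the article's only power statement. If the figure is wrong, nothing in the article supports its claim that the sample size is adequate, and the error makes the trial look more sensitive than it is.

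**Working it through.** **Inputs.** From Sample size: 20 evaluable women per group, four groups, power 0.80, alpha 0.05, 30 enrolled per group. From Statistical analyses: four-level ANCOVA with Tukey-Kramer tests. Two-sided testing is assumed because sidedness is not stated; one-sided results are given as well.

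**The plan's own figures.** The loss allowance reproduces: 20 / (1 − 0.33) = 29.9, so 30 per group. The 0.37 SD does not.

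**Two groups of 20, unadjusted.** Normal approximation: d = (z₀.₉₇₅ + z₀.₈₀) × √(2/n) = (1.960 + 0.842) × √(2/20) = 2.802 × 0.316 = 0.886 SD. The exact noncentral t gives 0.909 SD (one-sided 0.801).

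**Other sample sizes and actual power** (noncentral t, two-sided 5%):

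| Comparison | Detectable at 80% power | Power for 0.37 SD |
|---|---|---|
| 20 v 20 | 0.909 SD | 21% |
| 30 v 30 | 0.736 SD | 29% |
| 40 v 40 (evaluable women, strata pooled) | 0.634 SD | 37% |
| 60 v 60 (all enrolled, no loss) | 0.516 SD | 52% |

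One-sided testing with 60 v 60 still gives 0.457 SD.

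**Sample size that 0.37 SD would need.** n = 2 × 2.802² / 0.37² = 15.70 / 0.1369 = 114.7, so 115 per group (116 by noncentral t). One-sided by the normal approximation, 91.

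**Planned pairwise tests.** The Tukey critical value for four groups of 20 (76 df) is the studentized range quantile divided by √2, which is 2.627. Approximately, d = (2.627 + 0.842) × √(2/20) = 1.10 SD, and the noncentral t also gives 1.10. With 30 per group (116 df) the critical value is 2.607, and d = (2.607 + 0.842) × √(2/30) = 0.89 SD.

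**Covariate adjustment.** Adjustment multiplies the detectable difference by about √(1 − r²), where r is the covariate–outcome correlation. Reaching 0.37 SD needs r = √(1 − (0.37/0.909)²) = 0.91 with 20 v 20, or √(1 − (0.37/0.634)²) = 0.81 with 40 v 40. With 60 v 60 and no losses it needs √(1 − (0.37/0.516)²) = 0.70. The article claims no such correlation. It describes follicular fluid collection only at retrieval, so there is no baseline follicular value to adjust for.

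**Paired test.** With n = 20 the figure is 0.66 SD. With n = 60 it is 0.368 SD, but that contradicts 20 per group and would also need a baseline follicular sample.

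**Cohen's f.** For a four-group F-test the noncentrality is f² × N. With N = 80, 80% power needs f = 0.379. At f = 0.37 the power is 77.9%, and 21 per group would be needed. If the four means form two clusters of two, f = 0.37 puts them 2f = 0.74 SD apart. If two means are extreme and two lie midway, the extremes are f × √8 = 1.05 SD apart.

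**The case against.** **The number may be a mislabelled Cohen's f.** This is the best defence. The four-level model is the planned analysis, f is expressed in within-group SD units, and 0.379 is close to 0.37. It remains an inference, since the section mentions neither f nor an overall F-test. It would explain the number without making the sentence true, because the sentence claims a mean difference.

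**Twenty per group may be too few for this endpoint.** This stands in part. The 33% loss concerns oocytes, whereas the power statement concerns follicular fluid. The section on oocyte, cumulus cell and follicular fluid collection says that fluid is still obtained when no spare eggs are available. Up to 30 per group might therefore contribute, less blood-contaminated samples and dropouts. The size of the gap changes but the direction does not: 0.74 SD unadjusted and 0.89 SD under Tukey.

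**Stronger readings that the article does not support.**
- A reader might take 0.91 SD as the trial's true figure. It belongs to a single unadjusted two-group comparison. The planned pairwise tests give about 1.10 SD and the pooled treatment effect 0.63 SD.
- A reader might treat the 3.2 μg/ml gap as a ceiling on the treatment effect, because "This nutrition intervention is not designed for participants to lose weight". The same sentence allows that weight loss may occur, and the Discussion expects benefit through diet and exercise generally. Nothing establishes a ceiling.
- A reader might convert SD units into μg/ml and compare them with the gap. The article gives no SD, and a condensed article may leave it to the cited study, so any conversion would rest on a guess.
- A reader might say that a null result would be taken to exclude effects above 0.37 SD. A null result is read from its confidence interval, and the article plans no such inference.

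**Conclusion.** The stated detectable difference is wrong as written. No between-group comparison of means in this design reaches 0.37 SD at 80% power without a strong covariate that the article neither names nor claims. The true figures are about 1.4 times the stated one in the most generous two-sided case (0.516 / 0.37), 1.7 times for the pooled effect with 40 v 40 (0.634 / 0.37), 2.5 times for one unadjusted comparison of 20 v 20 (0.909 / 0.37), and 3.0 times under the planned Tukey tests (1.10 / 0.37).

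These figures assume equal group sizes, two-sided alpha 0.05, roughly normal outcomes with a common SD, and no gain from covariates. One-sided testing or more fluid samples narrows the gap without closing it.

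The statement of confidence loses its support. It rests on the 0.37 SD figure and on a contrast between normal-weight and obese women. Every participant has a BMI of 25 to 45, so that contrast is not an expected effect of the intervention. This does not show that the trial is too small for its purpose; it shows that the article's case for adequacy does not hold.

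**What to change.** Rewrite the Sample size paragraph for the analysis actually planned. At 80% power:

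- Tukey-Kramer pairwise tests at 5% family-wise error: about 1.10 SD with 20 evaluable women per group, or 0.89 SD if up to 30 per group give usable follicular fluid.
- Intervention v standard of care pooled over PCOS strata, two-sided 5%: 0.63 SD with 40 v 40.

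Say which n applies to follicular fluid and which to oocytes.

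If 0.37 was meant as Cohen's f for the four-group F-test, label it so, note that N = 80 gives f = 0.38 at 80% power, and state that f = 0.37 implies extreme group means about 0.74 to 1.05 SD apart.

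Remove the sentence expressing confidence in the sample size, or justify it against an expected intervention effect rather than the normal-weight v obese gap.

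The cost is one paragraph of text and a less favourable stated sensitivity. No patients are added and the design does not change.

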Models of diet-induced obesity in mice have shown that exercise improves, but does not reverse, damage imparted on oocytes as a result of a high fat diet [10]. A systematic review and meta-analysis of human studies found that exercise improved pregnancy rates (risk ratio 2.10, 95% CI: 1.32–3.35) in women with reproductive health problems like polycystic ovary syndrome (PCOS) [11]. Studies have also demonstrated promising maternal-fetal benefits of exercise during pregnancy such as improved physical fitness [12], more appropriate gestational weight gain [13], a decreased risk for preeclampsia and other pregnancy-specific diseases like gestational diabetes [14, 15], and decreased odds of macrosomia at birth without affecting the odds of growth-restricted, preterm, or low birth weight babies [12, 16, 17]. Studies have demonstrated that adherence to a Mediterranean diet, characterized by higher intake of unsaturated fats, lower intake of animal fats, and lower ratios of omega-6 to omega-3 fatty acids [18], is also associated with a reduced risk of many chronic diseases [19], improved fertility rates [odds ratio 1.4, 95% CI: 1.0–1.9] [20], as well as larger embryo yield in IVF [21], and better pregnancy outcomes [7, 20, 22, 23].

Despite the evidence of a healthier diet improving IVF procedure outcomes, there is little evidence on the molecular changes at the level of the oocyte or follicular fluid that occur due to alterations in diet, and virtually nothing is known about the impact of the combined effect of healthy diet and increased PA. Thus, we have designed a study with the primary objective of assessing the efficacy of a peri-conception nutrition and exercise intervention on mitigating obesity-associated changes in oocyte gene expression profiles and follicular fluid metabolites. Secondary objectives include determining the effect of the intervention on cumulus cells gene expression as well as the feasibility and acceptability of the intervention (using a standardized taxonomy [24]). To help address these objectives, overall metabolic health indices such as fitness, blood pressure, insulin sensitivity, triglycerides, C-reactive protein and interleukin-6 concentrations will be assessed.

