### Eligibility and recruitment

Criteria for study inclusion are women with a BMI between 25 and 45 kg/m^2^, age of 21 years or over, and planning to undergo in vitro fertility treatment. Participants reporting the following will be excluded from the study: pre-existing conditions (e.g. sexual transmitted diseases) that will affect the outcomes of the study as determined by the principal investigator; current use of recreational drugs, tobacco, nicotine, or alcohol; food allergies, food intolerances, or food preferences which would interfere with compliance to the meal plan; and contraindications to exercise or already meeting the Physical Activity Guidelines for Americans [8] (150 min moderate activity/week or 75 min of vigorous activity/week with resistance exercise on 2 or more days/week.

Recruitment of participants will be conducted by the AF&GA team using IRB-approved tools. Advertisements and information sheets will be distributed to eligible participants electing to undergo fertility treatments. Women who are interested in participating in the study can inform the AF&GA team, call the ACNC recruitment line, send an e-mail expressing their interest, or express their interest through the ACNC website. To establish eligibility for participation in the study, a standardized questionnaire will be administered by phone.

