### Consent and randomization

The informed consent process will educate potential participants about the research study through IRB-approved methods. Eligible participants will be contacted, and a copy of the informed consent will be provided to the participant prior to signing consent documents. A research team member will reach out to potential participants 2 days prior to the scheduled visit to perform a COVID-19 screening and answer questions on the intervention components of the study. At the first visit, the research team will review all study procedures and the informed consent documents with the potential participant. Participants will be given sufficient time to review the consent form, ask questions, and receive clarification prior to signing any documents. If eligible and interested in enrollment, informed consent will be obtained from the participants and documented.

Women will be randomized, with computer generated randomization, to a standard of care group (*N* = 60) and an intervention group (*N* = 60). Due to the high incidence of obese women with Polycystic Ovarian Syndrome (15–30%) [26], compared with other infertility diagnoses, women will first be classified into one of two strata based on the presence or absence of PCOS. Within each stratum, the proposed study will randomize the enrolled participants into either the intervention group (*N* = 30) or the standard of care group (*N* = 30). Thus, the potential for confounders of infertility, besides PCOS, should be equally distributed between the groups and not affecting the main outcome of interests. The study will have four experimental arms: PCOS-standard of care, PCOS-intervention, no PCOS-standard of care, no PCOS-intervention. Allocation will happen at the second visit (after consent and the collection of baseline measures) by providing the participant with an opaque, sealed envelope containing their allocation.

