#### Standard of care

Participants in the standard of care group will be provided with dietary and physical activity recommendations from the Dietary Guidelines for Americans at their first study visit and will follow the standard of care practice at AF&GA up to their retrieval procedures. Participants will not be required to wait 8 weeks prior to their retrieval procedures since no intervention is needed. If participants in the standard of care group plan to undergo a second oocyte retrieval cycle, they will be offered to join the intervention group at that time as a cross over design.

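### The CRP gap offered as reassurance about the sample size is between normal-weight and obese women, a contrast that the trial does not test

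*Protocol article*

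**What the plan says.** The Sample size section first gives a standardised figure: with 20 women per group, power 0.8 and p = 0.05, the trial is said to detect a difference of 0.37 SD in follicular CRP and insulin. It then offers one effect in natural units: "we found follicular fluid CRP differences of 3.2 μg/ml (2.7 vs. 5.9 μg/ml, respectively) between normal weight and obese women". The next sentence draws the conclusion: "Thus, we are confident that this sample size will be sufficient to detect clinically meaningful differences".

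The population and the comparison are fixed elsewhere in the article:

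- Eligibility and recruitment: "Criteria for study inclusion are women with a BMI between 25 and 45".
- Consent and randomization: "The study will have four experimental arms: PCOS-standard of care, PCOS-intervention, no PCOS-standard of care, no PCOS-intervention".
- Standard of care: control women "will be provided with dietary and physical activity recommendations from the Dietary Guidelines for Americans at their first study visit".
- Dietary intervention: "This nutrition intervention is not designed for participants to lose weight". The same sentence adds that weight loss could nevertheless occur.
- Background: the cited mouse work found that "exercise improves, but does not reverse, damage imparted on oocytes".

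The primary objective, in the Background, is to mitigate obesity-associated changes. No section states how large a between-arm difference in CRP is expected.

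**The concern.** The reassurance is drawn from a comparison of two populations, one of which cannot enter the trial. Both randomised arms come from the same BMI 25 to 45 population, which includes overweight women whom a normal-weight versus obese comparison does not describe. To see a mean difference of about 3.2 μg/ml between arms, the intervention would on average have to bring women from a level like that of the earlier obese group to the normal-weight level, with no movement in the control arm.

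Follicular fluid metabolites are a primary outcome. The Contingencies section already plans for finding no effect, by considering a longer intervention or additional exercise in later studies. If the size is believed adequate because of the 3.2 μg/ml gap, a null result could be taken as evidence that the intervention does not work, when a partial effect may simply have been too small for the trial to detect.

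**Working it through.** **Inputs from the Sample size section.** CRP 2.7 and 5.9 μg/ml, so the gap is 5.9 − 2.7 = 3.2 μg/ml; power 0.80; p = 0.05 (taken as two-sided, since the side is not stated); 20 analysable women per group; stated detectable difference 0.37 SD. No SD for CRP is given.

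**Step 1: the plan's own figure.** For a two-sample t-test, the detectable standardised difference is approximately d = (1.960 + 0.842) × √(2/n). With n = 20 this is 2.802 × 0.316 = 0.89; the exact t calculation gives 0.91. The stated 0.37 SD is not reproduced. At 0.37 SD, 20 per group gives about 21% power, and 80% power would need 115 per group. This arithmetic is a separate issue, but it means that 0.37 SD cannot be used to uphold the assurance.

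**Step 2: is 3.2 μg/ml the source of 0.37 SD?** Nothing in the section links them. Equating them would imply an SD of 3.2 / 0.37 = 8.6 μg/ml, which appears nowhere. The gap is supporting evidence, not the formula's input.

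**Step 3: the cited contrast beside the tested contrast.**

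| | Cited | Tested |
|---|---|---|
| Groups | normal weight vs obese | intervention vs standard of care, by PCOS stratum |
| Population | two BMI populations | one population, BMI 25 to 45 |
| What the difference measures | the whole gap | what 8 to 12 weeks of intervention adds to standard of care with advice |

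**Step 4: conditional size of the problem.** Take the SD at which the full gap has exactly 80% power with 20 per group: 3.2 / 0.909 = 3.52 μg/ml. This SD is an assumption that favours the plan, because it makes the design just adequate for the full gap. Power of the two-sided t-test with 20 per group:

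| Share of gap closed (assumed) | Difference, μg/ml | d = difference / 3.52 | Power |
|---|---|---|---|
| 100% | 3.2 | 0.91 | 80% |
| 75% | 2.4 | 0.68 | 56% |
| 50% | 1.6 | 0.45 | 29% |
| 25% | 0.8 | 0.23 | 11% |

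**Step 5: sensitivity to the SD, for half the gap (1.6 μg/ml).** The last column is 0.909 × SD, also shown as a share of 3.2.

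| Assumed SD, μg/ml | Power, 20 vs 20 | Power, strata pooled (40 vs 40) | Detectable with 20 vs 20 |
|---|---|---|---|
| 2 | 69% | 94% | 1.82 (57%) |
| 3 | 38% | 65% | 2.73 (85%) |
| 4 | 23% | 42% | 3.64 (114%) |
| 5 | 17% | 29% | 4.55 (142%) |

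With an SD of 2, pooling the strata gives ample power for half the gap. From an SD of 3 upwards it does not reach 80%.

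**The case against.** The strongest reply is that the size was never derived from 3.2 μg/ml. The section ties 20 per group to 0.37 SD, and at SDs of 2 to 5 μg/ml that is 0.74 to 1.85 μg/ml, or 23% to 58% of the gap. On its face, then, the plan already allows for partial closure. The first half of this stands: the gap is not the formula's input. The second half fails, because 20 per group detects about 0.91 SD and not 0.37 SD. Even if the standardised figure were corrected, the gap would remain the only evidence in natural units that the detectable difference matters clinically, and it would still come from another contrast.

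A reader might infer that 3.2 μg/ml is a ceiling on any intervention effect. The article does not support that. The BMI and PCOS mix of the earlier obese group is not shown, this trial admits women up to BMI 45 and plans half its women with PCOS, and baseline CRP could be lower or higher. Nor must every woman start at the obese level and normalise fully, since only the means matter. That the diet does not target weight loss is no limit on CRP either: weight loss may occur, and exercise is a separate component.

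It is also fair that the section names the two populations openly and never calls 3.2 μg/ml the expected difference between arms. The fault lies in the conclusion drawn from it.

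Finally, 20 per group reflects oocyte yield, and the article expects follicular fluid even where no spare oocyte is obtained. With 30 per group the detectable difference would be about 0.74 SD. That softens the power figures but does not make the cited contrast relevant.

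**Conclusion.** The concern holds in limited form. The statement that the size suffices for clinically meaningful differences is drawn from a gap between normal-weight and obese women, while the trial compares two randomised arms within one BMI 25 to 45 population and states no expected effect on CRP. The gap is a benchmark for roughly full normalisation and does not support the statement.

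The loss of power cannot be fixed without an SD. On the plan-favouring assumption of 3.52 μg/ml and 20 per group, it falls from 80% for the full gap to about 56%, 29% and 11% for three quarters, half and a quarter of it. The shares closed are also assumptions; the article gives none. It would go too far to say that the trial is shown to be underpowered by a particular factor, or that a specific smaller effect is to be expected. This is a misdirected justification that should be corrected, not a fault in allocation or in the primary tests.

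**What to change.** In the Sample size section:

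1. State that 3.2 μg/ml is a between-population benchmark and not the expected difference between arms.
2. Remove or qualify the sentence expressing confidence in the sample size.
3. Give instead the difference in μg/ml that 20 per group can detect, using the CRP SD from the sponsor's earlier study and a correctly computed standardised difference (about 0.91 SD for a two-sided t-test), and say what fraction of 3.2 μg/ml it represents.
4. State that a null result will be interpreted through the confidence interval of the between-arm difference, set against that benchmark.

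A formal estimate of the proportion of the gap closed is not advised. The historical gap has no stated uncertainty and the trial has no normal-weight group in which to re-estimate it. A BMI 30 and over subgroup would only be less precise.

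The cost is rewording and one calculation from data that the sponsor should already hold. No extra patients are needed. The stated assurance becomes less favourable.
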